### Specific Aims and Hypotheses

For the first aim, we intend to conduct an RCT of the BRAVE intervention by randomly assigning veterans with potentially hazardous drinking patterns, but who have not received recent treatment for drinking or any other behavioral health problem, to receive either the BRAVE intervention or a resources-only control condition. We hypothesize that BRAVE participants will drink less (fewer days per week, fewer drinks per occasion, and fewer binge drinking days), experience fewer negative alcohol-related consequences, and report more treatment readiness, preparatory behaviors, and initiation behaviors at 3, 6, 9, and 12 months post intervention, relative to control participants. For the second aim, we will determine for which subgroups the intervention works best. We hypothesize BRAVE participants who report more baseline barriers to care (eg, perceived public stigma beliefs that others would view them negatively for seeking care, not having time due to work or family responsibilities), baseline high levels of PTSD or depression symptoms, and higher baseline problematic alcohol use will benefit most from the intervention in terms of drinking reductions and treatment initiation outcomes. Sex (male and female) will be examined as an exploratory moderator, which expands on veteran work that traditionally examines male veterans only, which is important considering unique female-specific factors that affect treatment engagement [39].

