### Procedures

Participants will be recruited with the aid of a recruitment platform, BuildClinical, which uses machine learning and data mining procedures to target internet ads to recruit the sample population from a variety of general internet and social media sources (eg, Instagram, Facebook, Google, and health websites). BuildClinical uses targeted ad imagery and text to ensure we meet the recruitment needs of the study, including aiming for 10%-15% women veterans to match the growing number of post-9/11 women veterans. The pilot intervention study successfully enrolled 18% of women veterans [49]. Participants will click on ads displayed and be directed to a website with a description of the study. If interested, they can fill out a web-based screening form to assess eligibility and answer questions to help determine that they are not falsifying responses to gain access to the offered incentives. We have developed procedures to identify and exclude nonveterans from enrollment, which includes asking about first-hand knowledge through questions that must be consistent across responses (eg, branch, rank, pay grade, and job in the military must all make sense when considered together) and ensuring responses are identical when asked variations of the same question at different times throughout the survey. Once participants pass through the initial validation checks, we will call each potential participant to verify the information they provided (eg, ensuring phone responses match survey responses to items such as branch and rank). If the individual’s responses are deemed credible and they remain interested in participation, the individual will be enrolled as a participant following a discussion of the study procedures and consent document. Once enrolled, participants will fill out a baseline survey and then be randomized to one of two conditions: the BRAVE intervention or a resources-only control condition.

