We will test for significant effect moderation by the following variables: barriers to care, PTSD, depression, and severity of AUD symptoms. To explore moderation, we will use simple linear regression models for primary outcomes at each time point. We will include an interaction term between each potential moderator and the intervention indicator (BRAVE vs control). Significant interactions between the intervention group and these moderators will be plotted with appropriate values and interpreted. Simple slopes will be calculated for all significant interactions. Given our prior work and the large sample size, we expect to have adequate numbers of participants in each cell for moderation analyses and will use established cutoff scores on the PCL-5 (score 33 or higher vs under 33), PHQ-8 (scores 10 or higher vs under 10), and the AUDIT (scores 8 or higher vs under 8). We hypothesize that those with greater barriers, PTSD, depression, and severity of AUD symptoms will benefit most from the intervention. Sex (male or female) will be included as an exploratory moderator.

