#### Power Analysis

Given this study design (and standard *P*<.05; 2-tailed testing), we will have 80% power to detect small treatment effects between the groups; specifically, effects of d=0.22 at 3- and 6-month follow-ups and d=0.23 at 9- and 12-month follow-ups. For reference, our observed intervention effect sizes at 1 month post intervention in the pilot study were *d*=0.17 for average drinks, *d*=0.18 for binge days per month, and *d*=0.19 for consequences [49]. We have similarly found small effect sizes over 2 years of follow-up in other large-scale PNF studies [76-78]. We expect effect sizes to be small, though slightly larger than those in our prior work given we include a sample screening positive for hazardous alcohol use that could benefit from treatment, whereas prior work targeted general college students and young veterans drinking at less severe levels. As noted, given that this intervention targets those who may never have received care otherwise, small effects seen in brief interventions, such as this, are potentially clinically significant.

Our prior work evaluating treatment-seeking behaviors has found rates of preparatory and actual treatment-seeking by service members to increase by double following brief phone-based feedback [79]. Other work has similarly found rates of substance use treatment initiation to increase to upwards of 50% following in-person feedback–based approaches [80]; thus, we hypothesize that upwards of 50% of participants who receive the enhanced PNF will report actual treatment initiation at some point during the 12-month follow-up period. We will examine preparatory behaviors (ie, steps along the way to actual initiation) and motivation to seek care.

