Moderation analyses of this study could allow for the further tailoring of our treatment approach and better targeting of specific subgroups of veterans. That is, should our analyses reveal that veterans with specific clinical or demographic characteristics are more likely to evidence reductions in drinking and treatment-seeking behaviors, this could justify targeted dissemination of PNF interventions, like ours, to such veterans. On the other hand, should a subgroup of veterans be less responsive to BRAVE, researchers could consider further adapting such interventions to better target relevant symptom processes or demographic groups. Hypothetically, such an intervention could be tailored to better meet the needs of female or male veterans or could include modules specific to PTSD or depression symptomology.

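### The claim of adequate cell numbers for moderation is not supported by the trial's own power figures: a binary interaction must be at least twice the detectable main effect to be found with 80% power

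*Protocol article*

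**What the plan says.** The protocol article makes four statements that bear on moderation.

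- **Aim.** Specific Aims and Hypotheses says of the second aim that "we will determine for which subgroups the intervention works best". It gives directional hypotheses for barriers to care, PTSD or depression symptoms, and problematic alcohol use. Sex is labelled exploratory.
- **Adequacy.** The moderation paragraph of the Analytic Plan says: "Given our prior work and the large sample size, we expect to have adequate numbers of participants in each cell for moderation analyses". PCL-5, PHQ-8 and AUDIT are each split in two at a cutoff, and no cutoff is given for barriers. One arm-by-moderator term is tested in a linear regression at each time point.
- **Reporting.** The same paragraph says that significant interactions will be plotted and interpreted, and that "Simple slopes will be calculated for all significant interactions".
- **Power.** The Power Analysis section says "we will have 80% power to detect small treatment effects between the groups", namely "effects of d=0.22 at 3- and 6-month follow-ups and d=0.23 at 9- and 12-month follow-ups", under "standard *P*<.05; 2-tailed testing". It gives no interaction size, interaction power or cell count.

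The Procedures section sets the expected share of women, "including aiming for 10%-15% women veterans to match the growing number of post-9/11 women veterans". The Discussion says that if some subgroups respond better, "this could justify targeted dissemination of PNF interventions, like ours, to such veterans".

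**The concern.** A sample that is just large enough for a small main effect is not large enough for a difference between two subgroup effects of similar size. The adequacy sentence has no calculation behind it, and the one calculation in the article points the other way.

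Aim 2 is one of the trial's two aims, and the Discussion contemplates using it to target dissemination or adapt the intervention. Two misreadings are possible. A non-significant interaction may be taken as equal benefit, because the sample was called large enough. A significant one may be taken at face value, although an estimate must be large to reach significance at all.

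**Working it through.** **Inputs from the article.** Two-sided 5% test, 80% power, 400 randomised per arm, detectable main effect d=0.22 (3 and 6 months) and 0.23 (9 and 12 months).

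**Assumptions.** Outcomes in SD units, equal analysed numbers per arm, and the same moderator split in each arm. The PTSD, depression and AUDIT splits in this sample are not given, so a range is shown.

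**Step 1: recover the analysed number behind the power statement.** The constant is 1.960 + 0.842 = 2.802.

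- n per arm = 2 × (2.802/d)²
- d=0.22: n ≈ 324, which is 324/400 = 81% of those randomised
- d=0.23: n ≈ 297, which is 297/400 = 74%

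The article's main-effect figures therefore reproduce if retention is near 80% and 75%. Retention is not stated and is inferred here.

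**Step 2: compare the two standard errors.** For a binary moderator with share p in the smaller group:

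- SE(main) = sqrt(2/n)
- SE(interaction) = sqrt(2/(pn) + 2/((1−p)n))
- Ratio = 1/sqrt(p(1−p)), which is at least 2 for every p

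The ratio does not depend on retention. It is also unchanged if baseline adjustment reduces residual variance, because both standard errors then shrink alike.

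**Step 3: results at 3 months, n=324 per arm.** The detectable interaction is 2.802 × SE. The last two columns are for a true interaction of 0.22, that is, one as large as the whole detectable main effect. Overstatement is the mean absolute estimate among significant results, divided by 0.22.

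| Split p | Smaller cell, per arm | SE | Detectable interaction | Multiple of 0.22 | Power at 0.22 | Overstatement |
|---|---|---|---|---|---|---|
| 50% | 162 | 0.157 | 0.44 | 2.0 | 29% | 1.85 |
| 30% | 97 | 0.171 | 0.48 | 2.2 | 25% | 2.0 |
| 15% | 49 | 0.220 | 0.62 | 2.8 | 17% | 2.5 |
| 10% | 32 | 0.262 | 0.73 | 3.3 | 13% | 2.9 |

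At 9 and 12 months (n=297) the detectable interaction runs from 0.46 at 50% to 0.77 at 10%.

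**Step 4: the smallest estimate that can be significant.** This is 1.96 × SE: 1.96 × 0.157 = 0.31 at 50:50 and 1.96 × 0.262 = 0.51 at 10%. Both exceed 0.22, so any significant binary interaction will be estimated as larger than the whole detectable main effect.

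**Step 5: barriers as a continuous score.** Detectable interaction = 2.802 × sqrt(4/648) = 0.22 per SD of the score, or 0.44 between −1 and +1 SD.

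**Step 6: a strong pattern.** Suppose that all the benefit falls in a share p of participants and none elsewhere. The interaction is then the average effect divided by p. With an average of 0.22, power is 80% at p=50% (interaction 0.44) and 99% at p=30% (0.73). With an average of 0.17, the lowest pilot figure in the Power Analysis, it is 58% and 91%.

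**The case against.** Several points on the other side are fair.

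- **The sentence is about numbers per cell, not power.** That is literally so. But numbers are adequate only for a purpose, and the sentence names that purpose as the moderation analyses.
- **Moderation is already described as exploratory.** The Abstract and the moderation paragraph both use that language, and sex is explicitly exploratory. This reduces the problem but does not remove it: the aim itself says *determine*, and the other moderators carry directional hypotheses.
- **A strong moderator would be found.** This stands, as Step 6 shows, and the hypothesised direction is that more severe participants benefit more. A reader might infer that no plausible interaction is detectable, or that Aim 2 will certainly fail; the figures do not support either. But Step 6 needs zero benefit in half or more of the sample.
- **The small splits are not this sample's.** This stands for PTSD and depression. The Introduction's 10% to 30% describes post-9/11 veterans generally, whereas this trial enrols people who screen positive on the AUDIT. The 10% to 15% rows are documented only for sex. A reader might also put the multiple at about four, but against the plan's own 0.22 it stops at 3.3. It passes four only near a 10% split and against smaller, pilot-sized effects (0.73/0.17 = 4.3).
- **Nothing says that non-significant estimates will be withheld, or that a null result will be read as equal benefit.** Correct. The text fixes only which interactions are plotted, interpreted and given simple slopes, and fuller reporting may be in an analysis plan that is not shown. The Discussion's remarks on dissemination are conditional.

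A reader might also see the 10% to 15% aim for women as part of the defect. It is a recruitment aim, not a cap, and raising it to the pilot's 18% would still leave a detectable sex interaction of 0.57, so no change is asked for there.

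**Conclusion.** The concern holds in a limited form. The adequacy sentence is unsupported, and *determine* is stronger than the sample allows. The minimum of twice the detectable main effect follows from the 1:1 design and holds for any binary split. The higher multiples depend on the split. The absolute values rest on the analysed numbers inferred from the Power Analysis and on outcomes treated as continuous.

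Moderation of moderate size is more likely to be missed than found, and only a strong concentration of benefit would be detected reliably. The rule of interpreting only significant interactions favours overstated estimates. The primary comparison of the two arms is unaffected.

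**What to change.** 1. Replace the adequacy sentence with the detectable interactions over a stated range of splits, for example 0.44 at 50:50, 0.48 at 30% and 0.62 to 0.73 at 15% to 10%, with 0.22 per SD for barriers if that score is kept continuous. In the second aim, change *determine* to *explore*, in line with the Abstract and the moderation paragraph.
2. For every named moderator at the 3-month primary time point, report the interaction estimate with its 95% confidence interval, and the arm effect with its interval at each moderator level, whatever the significance. State that a non-significant interaction is not evidence of equal benefit.

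The cost is some wording and a few more reported estimates, with no extra participants. The downside is a less favourable statement of what Aim 2 can show.

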#### Power Analysis

Given this study design (and standard *P*<.05; 2-tailed testing), we will have 80% power to detect small treatment effects between the groups; specifically, effects of d=0.22 at 3- and 6-month follow-ups and d=0.23 at 9- and 12-month follow-ups. For reference, our observed intervention effect sizes at 1 month post intervention in the pilot study were *d*=0.17 for average drinks, *d*=0.18 for binge days per month, and *d*=0.19 for consequences [49]. We have similarly found small effect sizes over 2 years of follow-up in other large-scale PNF studies [76-78]. We expect effect sizes to be small, though slightly larger than those in our prior work given we include a sample screening positive for hazardous alcohol use that could benefit from treatment, whereas prior work targeted general college students and young veterans drinking at less severe levels. As noted, given that this intervention targets those who may never have received care otherwise, small effects seen in brief interventions, such as this, are potentially clinically significant.

Our prior work evaluating treatment-seeking behaviors has found rates of preparatory and actual treatment-seeking by service members to increase by double following brief phone-based feedback [79]. Other work has similarly found rates of substance use treatment initiation to increase to upwards of 50% following in-person feedback–based approaches [80]; thus, we hypothesize that upwards of 50% of participants who receive the enhanced PNF will report actual treatment initiation at some point during the 12-month follow-up period. We will examine preparatory behaviors (ie, steps along the way to actual initiation) and motivation to seek care.

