In an effort to reach veterans outside of VA settings, we designed and pilot-tested a single-session intervention [46] for a cohort of young adult veterans (ie, aged 18 to 34 years) who were recruited on social media websites. In the intervention, which targeted veteran drinkers who were not necessarily seeking treatment for alcohol-related concerns, veteran participants were shown normative data of their sex-specific veteran peers (ie, other male veterans and other female veterans) [47,48] to correct their overestimations of peer veteran drinking behavior and to provide a comparative reference for their drinking behavior (ie, to demonstrate that their veteran peers likely drink less than an individual may think other veterans drink, or less than they, in fact, do). In this pilot randomized controlled trial (RCT; ClinicalTrials.gov NCT02187887), we found small but significant intervention effects favoring the intervention 1 month post intervention on all prespecified drinking outcomes: past 30-day drinks per week (*d*=0.47), average number of drinks per occasion (*d*=0.17), binge drinking days (defined at 5 drinks in a row for males and 4 drinks in a row for females; *d*=0.18), and alcohol-related consequences (*d*=0.17) compared to control [49].

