### Participant Recruitment and Eligibility

The BRAVE intervention is designed for mobile phones with internet capabilities and is targeted toward young adult veterans. Though the intervention is designed for use on mobile phones, it can be accessed through computers and tablets. Given the focus on a younger veteran cohort, eligibility criteria include (1) US veteran who has been discharged or separated from the Air Force, Army, Navy, Marine Corps, or Coast Guard (participants could have also been in the reserves or guard units, but not on active duty), (2) between the ages of 18 and 40 years, (3) a score on the 10-item Alcohol Use Disorders Identification Test (AUDIT [54]) of 4 or greater (men) or 3 or greater (women), which represents cutoff scores to identify those who may benefit from interventions to reduce alcohol misuse, (4) no upcoming appointments at the VA or elsewhere to receive treatment for a behavioral health concern (such as depression, PTSD, or alcohol use concerns), and (5) no appointments in the past six months for behavioral health treatment at a VA or elsewhere. The purpose of these latter 2 criteria is to reach participants outside of traditional care settings (ie, those who may need care but who are not receiving it) and to measure the effect of the intervention on treatment initiation. Participants also need access to the internet via a computer, tablet, or phone; a working email address; and the ability to read and understand English. Based on these criteria, we will recruit 800 participants who will be randomly assigned to the BRAVE intervention (n=400) or a resources-only control condition (n=400) that presents resources for care seeking (eg, location of local VA and links for connecting with local veteran service organizations) without any personalized content.

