#### Primary Outcomes

Primary outcomes are drinking behavior (past 30-day frequency, quantity, and number of binge-drinking days), negative alcohol-related consequences, and treatment initiation. Three past 30-day drinking outcomes will be assessed through single-item self-reports: drinking days, average drinks per occasion, and binge drinking days. Alcohol-related consequences in the past 30 days will be assessed with the Short Inventory of Problems [68], which is modified from the Drinker Inventory of Consequences [69]. The treatment outcome will be measured as treatment initiation in the time period after the intervention (ie, post baseline). Treatment initiation is assessed with an item asking participants to indicate if they have seen a provider at a VA or non-VA care setting for therapy, counseling, support groups, hospitalization, or medications for any concerns related to alcohol or substance use (eg, if they sought help to drink less, or attended groups to stay abstinent from cannabis or other drugs) or mental health concerns (eg, to help with stress, anxiety, depression, nightmares) in the past 6 months (at baseline) and past 3 months (follow-ups). Providers are defined for participants as a mental health or behavioral health provider (eg, psychiatrist, psychologist, social worker, mental or behavioral health nurse, or other providers), a general medical provider (eg, primary care doctor, physician assistant, and nurse practitioner), or an addiction specialist (eg, addiction counselor). Care is specified as either in-person or via telehealth.

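### Five unranked primary outcomes at 3 months have no rule for success, and the stated 80% power is that of a single unadjusted test

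*Protocol article*

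**What the plan says.** - **Outcomes.** Under Primary Outcomes: "Primary outcomes are drinking behavior (past 30-day frequency, quantity, and number of binge-drinking days), negative alcohol-related consequences, and treatment initiation". That makes five: drinking days, drinks per occasion, binge days, consequences and treatment initiation. None is placed above the others.
- **Hypothesis.** Specific Aims and Hypotheses predicts benefit on the drinking, consequence and treatment outcomes "at 3, 6, 9, and 12 months post intervention, relative to control participants".
- **Time point and models.** The Overview of the Analytic Plan makes baseline to 3 months the primary time point and describes the later three waves as also of interest. The drinking outcomes are analysed by regressing latent growth factors on arm. Treatment initiation gets a categorical growth model plus a logistic regression at each wave.
- **Power.** Power Analysis uses "standard *P*<.05; 2-tailed testing" and states that "we will have 80% power to detect small treatment effects between the groups", namely "effects of d=0.22 at 3- and 6-month follow-ups and d=0.23 at 9- and 12-month follow-ups".
- **Sample size.** Under Participant Recruitment and Eligibility: "we will recruit 800 participants who will be randomly assigned to the BRAVE intervention (n=400) or a resources-only control condition (n=400").
- **Pilot benchmark.** For alcohol-related consequences, Background gives "and alcohol-related consequences (*d*=0.17) compared to control [49"], while Power Analysis gives "for binge days per month, and *d*=0.19 for consequences". Both cite the same pilot report at 1 month.

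The article gives no testing order, no adjustment across the five outcomes, and no statement that one, some or all of them must be significant.

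**The concern.** With five primary outcomes of equal standing, the conclusion depends on a rule that the article does not give. The Discussion looks ahead to what follows if the intervention shows efficacy, but nothing defines what would show it. Under one reading, a single significant outcome out of five is enough, and the 5% error rate applies to each test but not to the claim. Under the other, all five must be significant; the error rate is then safe, but the trial's power is well below the 80% quoted. The one power statement describes neither situation, because it is the power of one outcome tested alone at 0.05. At stake are the false-positive risk behind a claim of efficacy and the effect size that the trial can be said to detect.

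**Working it through.** **Inputs from the article:** 400 per arm, two-sided alpha 0.05, power 80%, d=0.22 (3 and 6 months) and d=0.23 (9 and 12 months), five primary outcomes, primary time point 3 months. **Assumed here:** correlations between outcomes and between baseline and follow-up, and the number analysed per arm, which is back-solved.

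**1. Reproducing the stated power.** Two-sample normal approximation, SD 1, one test: n per arm = 2 × ((1.960 + 0.842)/d)².
- d=0.22: 2 × (2.802/0.22)² ≈ 324 per arm, 324/400 = 81%.
- d=0.23: 2 × (2.802/0.23)² ≈ 297 per arm, 297/400 = 74%.
- With all 400 per arm, power would be 87.5% at d=0.22 and 90.2% at d=0.23.

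So the 80% matches one unadjusted test after some loss to follow-up. The stated d values are rounded: d from 0.215 to 0.225 corresponds to about 340 to 310 per arm (85% to 78%), and d from 0.225 to 0.235 to about 310 to 284 per arm (78% to 71%). The retention is therefore an inference and only approximate.

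**2. Error if any one of five counts.** Independent tests: 1 − 0.95⁵ = 22.6%. Correlated tests, simulated from a multivariate normal with two-sided 0.05 for each test:

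| Assumed correlation | All five equally correlated | Four drinking outcomes correlated, initiation independent |
|---|---|---|
| 0.3 | 20.8% | 21.5% |
| 0.5 | 18.3% | 19.8% |
| 0.7 | 14.8% | 17.4% |

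**3. Power if all five must succeed.** With 80% power on each, joint power is 0.8⁵ = 32.8% if independent, and about 44%, 51% and 59% at a common correlation of 0.3, 0.5 and 0.7.

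**4. Power if the family is controlled.** The first Holm step for five tests uses alpha 0.05/5 = 0.01, with critical value 2.576. With 324 per arm:
- Power at d=0.22: Φ(0.22 × √(324/2) − 2.576) = Φ(2.800 − 2.576) = Φ(0.224) ≈ 59%.
- Detectable d at 80% power: (2.576 + 0.842) × √(2/324) ≈ 0.27.
- With baseline adjustment at correlation 0.5, the residual variance is 1 − 0.5² = 0.75. Power is Φ(2.800/√0.75 − 2.576) = Φ(0.657) ≈ 74%, and the detectable d is 0.2685 × √0.75 ≈ 0.23.
- With all 400 per arm and no adjustment, power is about 70% and the detectable d about 0.24.

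These are figures for the strictest step. Once some outcomes have been rejected, Holm tests the rest at larger alphas, so power per outcome under Holm is at least as high as shown.

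**The case against.** **The rule may be elsewhere.** A journal article condenses a fuller plan, and a multiplicity procedure could sit in a document not shown. The 5% level appears only in parentheses, as an input to the power calculation. This has weight, and for the same reason the unstated retention and the absence of a power figure for treatment initiation are not held against the article. It does not remove the point. The article itself fixes five unranked primary outcomes and quotes power at an unadjusted 0.05. If an unseen plan adjusts alpha, the power statement needs requalifying; if it does not, the error question is open.

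**The hypothesis reads as a conjunction.** It predicts benefit on every outcome. If that is also the success criterion, error is not inflated. This is correct, and it makes the 15% to 23% range conditional on an any-one-of-five reading. The difficulty then moves to joint power.

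**A reader might count 20 tests**, five outcomes at four waves, and infer a much larger error rate. The article does not support that. The Analytic Plan makes 3 months primary; the formal tests for drinking outcomes are on growth factors; Cohen d by wave is offered for practical significance; and wave-by-wave tests of the main effect are planned only for treatment initiation. The confirmatory family is best read as five.

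**The 59% leaves out the planned use of baseline.** This is fair, so the adjusted 74% is given beside it. It depends on an assumed correlation.

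**The power sentence is not false.** As a statement about one outcome at one wave, it is consistent with plausible retention. The fault is that it is offered as the power of a trial with five primary outcomes.

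**Conclusion.** The concern holds for five outcomes at 3 months. If any one significant outcome is taken as efficacy, familywise error is 22.6% under independence and about 15% to 22% at assumed correlations of 0.3 to 0.7, roughly three to four times the nominal 5%. If all five are required, error is controlled, but power is about 33% to 59% when each outcome has 80%, over correlations from 0 to 0.7. With the family controlled, power at d=0.22 at the strictest step is about 59% unadjusted, or 74% with baseline adjustment at correlation 0.5, given about 324 per arm analysed. That number and both sets of correlations are assumptions.

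This should be fixed. It does not show that the trial will make a false claim, since the article does not say which reading applies. The conflict over the pilot effect for consequences (0.17 against 0.19) is a minor correction to a reference value and does not enter the power calculation.

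**What to change.** 1. Define the confirmatory family as the between-arm comparison at 3 months on each of the five primary outcomes, tested with Holm at two-sided 5%. Alternatively, name one primary outcome and make the other four secondary.
2. State explicitly that the 6-, 9- and 12-month results are secondary. This agrees with the primary time point already set in the Analytic Plan.
3. Restate power as power per outcome at the alpha that applies, using the authors' own retention assumption and saying whether baseline is adjusted for. With about 324 per arm, the detectable d at alpha 0.01 would be about 0.27 unadjusted, or about 0.23 with baseline adjustment at correlation 0.5.
4. Reconcile the two pilot effect sizes for consequences in Background and Power Analysis against the pilot report.

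The cost is wording in the analysis plan; no new data or participants are needed. The downside is a stricter threshold for each outcome and a less favourable stated detectable effect.
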